## Abstract

**Introduction:**

The number of people with diabetes mellitus is increasing globally and consequently so too is diabetic retinopathy (DR). Most patients with diabetes are monitored through the diabetic eye screening programme (DESP) until they have signs of retinopathy and these changes progress, requiring referral into hospital eye services (HES). Here, they continue to be monitored until they require treatment. Due to current pressures on HES, delays can occur, leading to harm. There is a need to triage patients based on their individual risk. At present, patients are stratified according to retinopathy stage alone, yet other risk factors like glycated haemoglobin (HbA1c) may be useful. Therefore, a prediction model that combines multiple prognostic factors to predict progression will be useful for triage in this setting to improve care.

We previously developed a Diabetic Retinopathy Progression model to Treatment or Vision Loss (DRPTVL-UK) using a large primary care database. The aim of the present study is to externally validate the DRPTVL-UK model in a secondary care setting, specifically in a population under care by HES. This study will also provide an opportunity to update the model by considering additional predictors not previously available.

**Methods and analysis:**

We will use a retrospective cohort of 2400 patients with diabetes aged 12 years and over, referred from DESP to the NHS hospital trusts with referable DR between 2013 and 2016, with follow-up information recorded until December 2021.

We will evaluate the external validity of the DRPTVL-UK model using measures of discrimination, calibration and net benefit. In addition, consensus meetings will be held to agree on acceptable risk thresholds for triage within the HES system.

**Ethics and dissemination:**

This study was approved by REC (ref 22/SC/0425, 05/12/2022, Hampshire A Research Ethics Committee). The results of the study will be published in a peer-reviewed journal, presented at clinical conferences.

**Trial Registration number:**

ISRCTN 10956293.

STRENGTHS AND LIMITATIONS OF THIS STUDYThe model will be externally validated in the secondary care setting in which it is intended to be used.Extracting the data (not using an existing dataset) ensures the sample size will be large enough for the aims.Retrospective cohort design means data can be extracted relatively quickly at minimal cost.Opportunity to update the model to include additional predictors, which may improve predictive performance.As data are being collected retrospectively, some predictor variables and outcomes may be missing for some patients or trusts. This will be dealt with by using multiple imputation where possible.

## Introduction

Diabetes mellitus is one of the most common chronic conditions affecting nearly 4.8 million people in UK as of 2019.^1^ With the prevalence rising each year,^2^ there is an ongoing global and UK wide increase in the number of people with diabetes mellitus^3–5^ and consequently diabetic retinopathy (DR). Our study estimated about 1.4 million with any DR and 0.54 million with referable stage DR^2^ in 2017. The detection of DR has also improved through wider population screening, further increasing the demand for hospital eye services (HES).^6^ Diabetes is a major public health concern and uses a significant proportion of the NHS budget, much of which is spent treating the complications of diabetes.^7^ These complications affect blood vessels in the heart, brain, kidney and eyes.^8^ Diabetes is the fourth-leading cause of preventable vision loss in the UK,^9^ and therefore, patients with diabetes are screened regularly for signs of DR. Screening services are organised by the Diabetic Eye Screening Programme (DESP) for patients without DR or with background DR. However, when a patient develops clinical signs of referable retinopathy, including preproliferative DR (R2), proliferative DR (R3) and/or diabetic maculopathy (M1), they are referred to HES or surveillance clinics for closer observation and treatment to prevent vision loss. The patients’ flow within the NHS is depicted in the figure 1.

**Figure 1 F1:**
[figure not shown]
Patient flow diagram (there may be local variations in practices). DESP, Diabetic Eye Screening Programme; HES, hospital eye services; M0, No Maculopathy; M1, Maculopathy present; R0, No retinopathy; R1, Background retinopathy; R2, preproliferative retinopathy; R3, proliferative retinopathy; STR, sight threatening retinopathy; VEGF, vascular endothelial growth factor.

Most referrals made to HES (50%–78%) will not yet require treatment.^10 11^ Among those that will require treatment, such as patients with diabetic maculopathy, the patients’ condition may be subthreshold (under 400 µm foveal thickness) for treatment and remain so for a period of time. Patients with preproliferative retinopathy are not offered any treatment and are monitored every 3–6 months until they progress to the proliferative retinopathy stage, at which point they receive treatment. Consequent overburdening of HES, combined with under-resourced services may be causing delays in patients being seen and causing harm especially in the higher-risk patients.^12^ Therefore, this bottleneck urgently needs addressing. We propose to mitigate this risk of harm to patients by stratifying patients referred to HES according to their risk of requiring treatment or losing their vision using a clinical prediction model. This would enable higher risk patients to be prioritised and seen sooner.

Clinical prediction models are statistical models that use multiple predictor variables to predict the risk of a clinical outcome.^13^ They can be used by clinicians to stratify care by risk groups based on the predicted probabilities from the model. The DESP uses risk stratification studies to inform suitable screening intervals.^14^ There are also prediction models to identify patients at the highest risk of developing referable DR,^10 15 16^ validated in a UK population.^17^ However, there are currently no such validated prediction models that can be used to stratify care according to risk in patients under the care of HES. Once validated, the Diabetic Retinopathy Progression model to Treatment or Vision Loss (DRPTVL-UK) model could help HES prioritise patients at high risk of vision loss, and to determine suitable follow-up intervals based on an individual’s risk.

The current length of follow-up intervals used within HES is based on the probability of disease progression from a study conducted in the late eighties^18^ and not based on the patient’s individual risk. We therefore aim to predict the progression of DR to treatment stage, to direct resources toward higher-risk patients so that they are followed up and treated before vision failure occurs. We propose that use of a validated risk prediction model will facilitate evidence-based decisions and thus reduce the chance of harm to higher-risk patients.

There are two recent systematic reviews of existing models for predicting the progression of DR among the DESP population.^15 19^ A review by this group of researchers found a total of 14 predictive model development studies of which 11 had been internally validated, 8 had been externally validated and only three without risk of bias.^15^ In a more recent review, there were 16 model development studies for an outcome of referable DR.^20^ Based on these two reviews, it was concluded that none of the existing models were intended for our target population (patients under care of HES/surveillance clinics) and none used the clinically important outcomes of interest (including contemporary treatment modalities and vision loss). Therefore, a prediction model that could be used to identify patients with a higher probability of requiring treatment or at high risk of loss of vision for HES was needed.

In brief, the DRPTVL-UK model was developed in anonymised, retrospective primary care data from IQVIA Medical Research Data (IMRD). From predictors identified in our systematic review,^15^ we selected a set of 19 clinically meaningful candidate predictors of DR progression using the Nominal Group Technique.^21^ A prediction model was then developed considering 15 of the 19 candidate predictors for inclusion based on availability in the dataset.^22^ After variable selection, the final model included seven predictors, namely (1) retinopathy stage, (2) glycated haemoglobin (HbA1c), (3) estimated glomerular filtration rate (eGFR), (4) total serum cholesterol, (5) systolic blood pressure and drug use of (6) insulin or (7) statins. The DRPTVL-UK model demonstrated moderately good discriminative performance (C-statistic=0.74) and very little optimism (0.004) in the internal validation due to the large sample size (13 691 patients).

### Rationale

We now need to assess the model’s predictive performance in a secondary care population to ensure it performs adequately to identify patients at high risk of treatment or vision loss in an HES setting. If this model performs well for predicting risk at time points up to 2 years in the external validation using HES/surveillance clinic data, we propose that it could be used to prioritise individuals at higher risk of vision loss and potentially inform the length of the follow-up intervals after referral to HES/surveillance clinics.

### Objectives and outcome measures/endpoints

The overall aim is to externally validate the multivariable risk prediction model we previously developed, recalibrating to the secondary care population if necessary and updating with additional predictor variables if necessary. The primary objectives are to:

Assess the external validity of the DRPTVL-UK model for predicting the risk of need for treatment or vision loss up to 2 years after referral in a hospital-based DR population by assessing model calibration, discrimination and net benefit.Evaluate whether recalibration of the baseline hazard or linear predictor (combination of predictor effects) improves predictive performance in an HES/surveillance clinic population and whether including additional predictors improves the model’s predictive performance in this population.

Secondary objectives are to:

Assess the DRPTVL-UK model’s external validity in the subgroup of patients with preproliferative DR (R2) or M1.Validate the model across several time points up to 2 years to assess whether it could be used to inform follow-up intervals after referral into HES or a surveillance clinic.

Parallel with the validation, there will be two consensus meetings of expert clinicians and patients to determine how the model can be implemented in practice and establish clinically meaningful thresholds for use.

## Methods and analysis

This prognostic study has been guided by the PROGRESS framework (theme 3 for prognostic models) and will be reported according to the TRIPOD Statement (Transparent Reporting of a multivariable prediction model for individual prognosis or diagnosis).^23^ The study started on 1 July 2022, with data extraction planned to start on 1 April 2023. Study is scheduled to end by the end of December 2023.

### Design and data sources

This retrospective cohort study will use patient data collected from HES/surveillance clinic and other related databases/patient notes from three NHS trusts. Where required information is not available for extraction from the hospitals’ notes, it will be obtained from surveillance clinics if available (and vice versa) by the participating NHS trusts.

### Patients and public involvement

Patients and the public have been involved in the design of this study (see online supplemental appendix 1 for details), and will be involved in the conduct, reporting and dissemination of this research.

10.1136/bmjopen-2023-073015.supp1Supplementary data

### Study population

The cohort will include type 1 and type 2 patients with diabetes, aged 12 years and over (as patients enter the screening programme from age 12), referred into HES or surveillance clinics with referable DR from DESP for close monitoring and treatment. Data will be collected from three NHS trusts for all patients within the catchment areas of Sandwell and Birmingham, Sunderland or Sussex NHS trusts. Records will be extracted for patients first entering the services between 1 January 2013 and 31 December 2016, with follow-up information extracted up to 31 December 2021. The Birmingham trust cares for an ethnically and socioeconomically diverse range of communities and was chosen to ensure equality, diversity and inclusion. The Sussex trust provides secondary care to a less diverse population and Sunderland is a primarily Caucasian population.

Patients with the specific outcome of retinopathy treatment or vision loss at referral or those referred for reasons other than retinopathy will be excluded. Patients objecting to their information being used (through a local or national opt out scheme) will also be excluded. Data flow and management stages are given in figure 2.

**Figure 2 F2:**
[figure not shown]
Data flow diagram. CAG, Confidentiality Advisory Group; NHS, National Health Service; PI, Principle investigator; R & D, Research and Development; SASH, Surrey and Sussex Healthcare NHS Trust; STS, South Tyneside and Sunderland NHS trust; SWBH, Sandwell and West Birmingham Hospitals NHS Trust.

### Sample size

A minimum of 200 outcome events are required for external validation using current guidance for survival outcomes.^24^ Every trust receives approximately 200 referrals per year and we expect to have 4 years’ worth of data available for each trust. Therefore, we expect to have approximately 2400 patients from across the three trusts to ensure a minimum of 200 outcomes. Recruitment will stop once the target number is reached.

Using conservative estimates from our development data, we expect 15% of those referred to develop the outcome of interest within 3 years follow-up,^22^ providing at least 360 outcomes in the data that we will collect. For model updating, we will use the method of Riley *et al*^25^ to calculate the minimum sample size required, assuming an event rate of 0.05 per year, mean follow-up of 3.23 years, a default Nagelkerke R^2^ of 0.15 and 19 candidate predictors considered in the model. A minimum of 1810 patients are required with 293 outcome events to target a shrinkage factor of 0.9 ensuring minimal overfitting to the data.

### Data extraction

A data extraction sheet has been prepared using Microsoft Excel and will be piloted prior to use within each trust. Data will be extracted for all predictors at baseline (first HES appointment after referral) and visual acuity level will be collected at each follow-up appointment. Data will continue to be extracted until an outcome of interest occurs, death, lost to follow-up or the end of the study period (31 December 2021).

Personal information such as date of birth (for age calculation), date of diabetes diagnosis and date of death (for censoring or competing risks analysis) will be extracted. However, all the personal identifiable information will be removed after age, diabetes duration and follow-up durations have been calculated.

### Outcomes

The primary outcome for this study is time to first treatment for DR or vision loss. Time will be calculated from referral to HES (baseline is first appointment) until the date of first treatment or vision loss. Time to death will also be recorded and treated as a competing risk if necessary.

### Predictor variables

The previously developed DRPTVL-UK model included seven predictors measured at the time of or close to referral, namely (1) retinopathy stage, (2) HbA1c (mmol/mol), (3) eGFR (mL/min/1.73 m^2^), (4) total serum cholesterol (mmol/L), (5) systolic blood pressure (mm Hg) and drug use of (6) insulin for (7) statins.

Some candidate predictors like the Early Worsening, high non-attendance rate, pregnancy and visual acuity were not previously available in the IMRD database used to develop the model but will be collected from the three trusts. Their definitions are in online supplemental appendices 2 and 3.

### DRPTVL-UK model

We previously developed and internally validated the DRPTVL-UK for the purpose of predicting the risk of vision loss and blindness or need for treatment in patients with referable DR. The model had good discrimination (C-statistic=0.74) and very little optimism in the internal validation. The model^22^ was developed in a primary care population and now needs external validation in the HES/surveillance clinic population, in which it is intended to be used.

The DRPTVL-UK model was developed using Cox regression and later refitted using a flexible parametric approach to obtain the baseline hazard function over time. The model can be used to predict the absolute risk of progression from referable DR to treatment or vision loss occurring within a 2-year period, based on an individual’s risk factor values. Thorough evaluation of the model’s external validity and net benefit is now required to establish whether the model is suitable for use in clinical practice in HES/surveillance clinics.

The DRPTVL-UK model can also be used to predict the time at which an individual reaches a particular risk threshold (to be agreed in a consensus meeting of clinical experts and patients planned after final analysis) which may be useful for determining appropriate follow-up intervals after referral to HES/surveillance clinics. This will be evaluated as a secondary objective.

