### Clinical benefit

We will also evaluate the clinical benefit of the model using decision curve analysis in which the net benefit of using the model at different threshold probabilities is plotted and compared with strategies of intervention for all (following up everyone more frequently) or intervention for no-one (no-one followed up more frequently).^31^

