### Clinical consensus

Alongside the statistical analysis, clinical consensus workshops will take place to help determine clinically meaningful threshold probabilities for net benefit analysis and for use of the model in practice. This will include discussion and agreement on a suitable threshold for identifying higher risk patients and potential thresholds for determining the follow-up intervals, prior to decision curve analysis. After the results of the external validation including the decision curve analysis are available, they will be presented to the ophthalmic expert committee panel for discussion on how the model can be implemented.

The consensus process was first used in the USA in the early 1970s to address the National Institutes of Health development programme to seek agreement on the safety and efficacy of medical procedures, drugs and devices.^33^ Consensus development meetings were introduced to the UK health system to discuss healthcare policies and its implementation in clinical practice.^34^

The consensus process will be used in this expert group to reduce the range of potential options presented to facilitate joint decision making by the group on the most appropriate choice of the model implementation strategies. The consensus process will help us evaluate the list of options and combine them if an overlap is noted between different options. It can also accommodate the inclusion of further options, check for redundancy between included options and reach agreement through sharing information and knowledge of the participants.^35^ The consensus process described below also enhances the critical thinking of the key stakeholders and facilitates joint decision making of the diverse groups.^36^ Communication and cooperation between participants are key to reach successful agreement on the options discussed and to increase the chances of wider acceptance for implementation.^37^ Here, we aim to reach an agreement on participants’ opinions on the various options under consideration.

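### The follow-up-interval risk threshold is to be agreed after the final analysis in one section and before decision curve analysis in another

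*Protocol article*

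**What the plan says.** Four sections of the protocol article bear on when thresholds are set.

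- *DRPTVL-UK model*: the model can predict when an individual reaches a given risk threshold, "which may be useful for determining appropriate follow-up intervals after referral to HES/surveillance clinics". That threshold is "to be agreed in a consensus meeting of clinical experts and patients planned after final analysis". The paragraph closes by making this use of the model a secondary objective to be evaluated.
- *Clinical consensus*: workshops held alongside the statistical analysis will "help determine clinically meaningful threshold probabilities for net benefit analysis and for use of the model in practice". Their content is "discussion and agreement on a suitable threshold for identifying higher risk patients" together with "potential thresholds for determining the follow-up intervals, prior to decision curve analysis". A later step follows: "After the results of the external validation including the decision curve analysis are available, they will be presented to the ophthalmic expert committee panel", where the discussion is about how to implement the model.
- *Objectives and outcome measures/endpoints*: "Parallel with the validation, there will be two consensus meetings of expert clinicians and patients". It does not say which of the two meetings fixes the thresholds.
- *Clinical benefit*: in the decision curve analysis, "the net benefit of using the model at different threshold probabilities is plotted", with comparison against more frequent follow-up for everyone and for no one.

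**The concern.** A threshold used to judge a model should be fixed by people who have not yet seen how the model performs. Clinical consensus follows that principle. The DRPTVL-UK model section, for the interval threshold, does not. If its wording governs, the panel may already know calibration, discrimination and net benefit when it decides which risk level should drive follow-up intervals. Performance then reported at that level would no longer be performance at a pre-specified point, and a reader of the results paper could not tell which order had been followed.

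There is also a practical problem. Evaluating the time at which patients reach a threshold requires the threshold. If it is agreed only after the final analysis, that evaluation either drops out of the final analysis or is added later with results known.

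**Working it through.** No arithmetic applies. The point concerns the order of events and depends on no sample size, event count or effect size. The check is a comparison of the texts.

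1. **Is it the same threshold?** The DRPTVL-UK model section speaks of the risk level used to derive follow-up intervals. Clinical consensus names follow-up-interval thresholds explicitly, alongside the high-risk threshold. The interval threshold therefore appears in both, and the difference cannot be explained as two separate quantities.

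2. **Can both timings hold?** Net benefit belongs to the first primary objective, and decision curves are listed among the performance measures under *External validation of the DRPTVL-UK model*. Taking the final analysis to include the planned validation measures, a meeting after it is also a meeting after decision curve analysis. One section therefore sets the interval threshold after the decision curves, and the other before them.

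3. **Does the Objectives section settle it?** No. Meetings in parallel with the validation are consistent with workshops alongside the analysis, so that section does not conflict with Clinical consensus. Because it does not assign threshold-setting to either meeting, it does not resolve the conflict.

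4. **Is the DRPTVL-UK model section consistent with itself?** Only in part. The secondary objective as listed under Objectives, validation at several time points up to 2 years, needs no threshold and can proceed. The predicted time to reach a threshold, which this section also says will be evaluated, cannot be assessed in an analysis that precedes agreement on the threshold.

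5. **Which results depend on the order?**

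| Result | Depends on when the threshold is agreed? |
|---|---|
| Harrell's and time-dependent C-statistics | No |
| Calibration slope, observed/expected ratio, calibration plots | No |
| Decision curve over the range of thresholds | No |
| High-risk (triage) threshold and net benefit at it | Timed only in Clinical consensus, before the decision curves |
| Interval threshold, and performance quoted at it | Yes; the two sections conflict |

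**The case against.** The strongest defence is a two-stage reading: candidate values before the decision curves and a final choice afterwards. It has some support. Two meetings are planned, the pre-analysis interval values are described as potential, and the voting procedure in Clinical consensus allows risk groupings to be sent back for refinement. But the article never states this sequence. Clinical consensus puts agreement, as well as discussion, before decision curve analysis, and it confines the post-results session to implementation. The reading is a plausible repair and needs to be written down.

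A second objection is that little depends on the order. Most of this stands. No success criterion is tied to net benefit at one agreed threshold, the whole curve is plotted, and suitability for follow-up intervals rests largely on calibration over time and on predicted against observed survival curves.

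A reader might infer more: that the threshold at which net benefit is judged will be picked where the model already looks best, so that the reported net benefit is biased upward. The documents do not support that. The parenthesis in the DRPTVL-UK model section covers only the interval threshold; the net-benefit and triage thresholds are timed only in Clinical consensus, before the analysis. Upward bias would also require the panel to choose the best-looking point, whereas the described process is a vote by clinicians and patients on a nine-point scale with a 70% rule. Seeing the results first is possible under one section; selecting on them is conjecture.

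**Conclusion.** The contradiction is real and stands in the current text, but it is narrow. It concerns the follow-up-interval threshold. If the DRPTVL-UK model section is followed, that threshold may be chosen with validation results in view, and the time-to-threshold evaluation cannot form part of the final analysis. If Clinical consensus is followed, neither problem arises. The full decision curve, the C-statistics and the calibration measures are the same either way.

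The size of any bias in performance quoted at the interval threshold cannot be computed from the documents. The conclusion rests on one assumption, that the final analysis includes the decision curve analysis. Its place in the primary objective and among the validation measures makes this the natural reading.

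**What to change.** Reconcile the DRPTVL-UK model section with Clinical consensus. Replace the parenthesis with a statement that the thresholds, or a narrow range of them, are agreed and recorded at the first consensus meeting, before the panel sees any validation or decision curve result. Say in the same place that the later meeting deals with implementation, and that any threshold changed there will be reported as post hoc.

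The change settles only when the thresholds are fixed; their values remain for the panel. It costs about a sentence of text and the ordering of two meetings already planned, and needs no additional data or analysis.
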